## Background

The success of irradiation in patients with localized prostate cancer correlates with the administered dose [1-5]. This is well known for patients with an intermediate risk profile and could also be found recently for patients with a low risk profile (Gleason score < 7; PSA < 10 ng/ml) [6]. Limitations for using higher doses are due to an increase of complication rates in particular to the rectum (bleedings, fistula, ulcer), urethra (stenosis) and bladder (chronic cystitis).

The rate of adverse effects is not only dependent on the dose but also on the radiation technique used. An earlier randomized study found that the rectum toxicity was lowered significantly when applying 3D-CT based radiation planning compared with simulator based planning [7]. In a dose escalating study at the MD Anderson, Pollack and co-workers found a volume dependency of the rectum toxicity (rectum volume irradiated with > 70 Gy, toxicity of grade II or higher after 5 years was 13% or 51% by ≤25% or >25% rectum volume, respectively [8]. Due to the use of intensity modulated radiotherapy it is possible to increase the doses up to 76–81 Gy whereas the adverse effects could, in comparison to 3D conformal radiotherapy, be lowered significantly using the same dosage reaching the level obtained with radiation series giving a total dose of 64–70 Gy. This monocentric historical comparison showed also a significantly higher cure rate [5].

Radiation biological considerations act on the assumption that the α/β value (tissue specific constant specifying the tissues’ sensitivity for the possibility of developing a late toxicity if single doses are increased) of the prostate cancer cells is low [9]. Since the assumed α/β value of 1.5 Gy for prostate cancer cells is clearly below the α/β values of bladder (α/β value 4.0) and rectum (α/β value 3.9), a radiation biological more effective dose could be administered due to increased single doses without increasing risks of late adverse effects. At the same time, the overall treatment time is shortened. This radiation biological hypothesis was confirmed in a study of 770 patients receiving a total dose of 70 Gy in 28 fractions, single doses of 2.5 Gy where biochemical recurrence free survival was 83% after 5 years for all risk groups, 95% for the low risk group with only 2% acute and late grade 3 or higher toxicity [2].

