### Evaluation of safety

In radiooncology we differentiate between acute and chronic adverse effects. Acute events are defined to arise within 6 weeks after end of treatment. Data of acute and chronic toxicities are collected during and after treatment on the basis of the NCI-CTC-AE (National Cancer Institute Common Terminology Criteria for Adverse Events) version 4.02 classified into

• Grade 1 = mild; clinical observation; intervention not indicated

• Grade 2 = moderate; minimal, local intervention indicated

• Grade 3 = severe; hospitalization; not immediately life-threatening

• Grade 4 = life-threatening

• Grade 5 = death related to AE

A safe feasibility is defined in this study if no grade 3 toxicity or higher is occurring from beginning of therapy to 6 weeks after the end of treatment without drop out from treatment (see next section). The time till the presentation of a > grade 2 toxicity is another, but secondary, endpoint. All toxicities > grade 2 must be reported the safety board.

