### Statistics

The primary objective of the pilot study is to demonstrate the safety and feasibility of the study treatment on the basis of the incidence of grade 3 or higher NCI-CTC AE toxicity and/or a termination of the planned therapy made of any reason. This secure feasibility (SF) is given when from the start of radiation therapy for up to 6 weeks after completion, not any grade 3 or higher toxicity occurred (including toxicity-related death, grade 5) and if the therapy was not stopped due to any other reason, e.g. due to any toxicity (grade 1–4). Taking into account the published very favorable results, the percentage of failure is assumed to be very small and is set to 2.5%, such that the target rate of the SFR was set to 97.5%.

Two co-primary study hypotheses are derived from the questions: a) Is the toxicity of carbon ion irradiation (arm B) non-inferior compared to standard radiation? b) Is the toxicity of the proton irradiation (arm A) non-inferior compared to standard?

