Formerly the two hypotheses are indepently test using the nullhypothesis Ho: SFR < 87.5% versus H1: SFR ≥ 97.5%, respectively, for each arm. The decision on the study success is defined for each arm separately. Assuming a type I error of alpha =10% and a power of at least 90% the study needs to recruit per arm n = 41 evaluable patients. This sample size calculation based on the PASS program (Number Cruncher Statistical Systems, October 24 2005, http://www.ncss.com/) and the procedure of Blackwelder (1982) for non-inferiority trials [19]. To replace drop out cases (drop out between consent and the start of treatment or for any other reason), per arm n = 46 patients will be recruited into the study such that a total of N = 92 patients is required. Randomization is performed in blocks of lenths 4 stratified by one dichotomized factor (presence/absence of anti-hormonal therapy during radiation). GS and PSA values will be used for defining post-randomization strata. The analysis of the primary endpoint will be performed by means of one-sample binomial testing. As describing parameters the 97.5% and the 90% confidence limits of the SFR are calculated. NCI-CTC adverse events will be evaluated. PSA-PSF, OS and duration of treatment or study participation are described by means of empirical survival functions. QoL will be evaluated using EORTC QLQ-C-30 guidelines. No formal interim analysis is planned, however, recruitment will be put on hold when the number of failures is larger than 4 in one arm for a discussion of the future of the study in the study team and the Institutional Review Board.

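### The recruitment hold counts only events up to 6 weeks after treatment, so late grade 3 or higher toxicity cannot trigger it

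*Protocol article*

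**What the plan says.** The Statistics section of the protocol article plans no formal interim analysis but states that "recruitment will be put on hold when the number of failures is larger than 4 in one arm", so that the study team and the Institutional Review Board can discuss how to proceed. That sentence does not define a failure. Earlier in the section, secure feasibility requires that "from the start of radiation therapy for up to 6 weeks after completion, not any grade 3 or higher toxicity occurred" and that therapy was not stopped. Failure is then used as its complement: "the percentage of failure is assumed to be very small and is set to 2.5%, such that the target rate of the SFR was set" at 97.5%. Evaluation of safety gives the same 6-week window and ends the acute period at the same point.

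Later toxicity is handled elsewhere. Work-up schedules toxicity assessments at 6 weeks and at 6, 12, 18 and 24 months, with yearly contact afterwards. Evaluation of safety makes time to toxicity above grade 2 a secondary endpoint and adds: "All toxicities > grade 2 must be reported the safety board". That sentence has no time limit. It also names no threshold and no consequence for recruitment. Duration of the study sets recruitment at two years.

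**The concern.** The safety question that motivates the trial is mainly about late harm. The Abstract and Background justify larger fractions by arguing that late effects in bladder and rectum should not increase, and they define the α/β value as sensitivity to late toxicity. Background says that higher doses are limited by an "increase of complication rates in particular to the rectum (bleedings, fistula, ulcer), urethra (stenosis) and bladder (chronic cystitis"). The carbon-ion benchmark it quotes is the absence of late grade 3 or higher toxicity in 176 patients, and the Discussion uses the Japanese results to support the 2.5% standard. For protons, the authors state that they could identify no hypofractionated prostate data.

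The one rule that pauses recruitment at a fixed number nevertheless closes its count where the late period begins. With two years of accrual, early patients are well into late follow-up while others are still being enrolled. A cluster of severe late events in one arm would leave the count unchanged.

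**Working it through.** **1. What failure means.** The hypotheses are "Ho: SFR < 87.5% versus H1: SFR ≥ 97.5%, respectively, for each arm", tested by a one-sample binomial test with 41 evaluable patients per arm, type I error 10% and power of at least 90%. With failure as the complement of the 6-week endpoint, the stated size reproduces exactly. Success at no more than 2 failures in 41 gives:
- type I error P(X ≤ 2 | 41, 0.125) = 0.0989
- power P(X ≤ 2 | 41, 0.025) = 0.917

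So failure has a definite meaning in the design: an event up to 6 weeks. The hold sentence gives it no other. At a 2.5% failure rate the hold (5 or more) fires with probability 0.003 for 41 patients and 0.006 for 46. At 12.5% it fires with probability 0.59 and 0.70.

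**2. How much late follow-up accrues during recruitment.**
- From the protocol: 46 patients per arm, 24 months of recruitment, 4 weeks of treatment, late period from 6 weeks (1.5 months) after treatment.
- Assumed: uniform accrual, and d = 1 to 2 months from enrolment to end of treatment.

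The number reaching m months after treatment before recruitment closes is 46 × (24 − m − d)/24:
- m = 6: 31 to 33 patients
- m = 12: 19 to 21 patients
- m = 18: 8 to 10 patients

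**3. Share of late events known while recruitment is open.** If events spread evenly from 1.5 to 24 months after treatment, the share is (24 − d − 1.5)² / (2 × 24 × 22.5). With d = 1.5 this is 441/1080 = 0.41. A separate calculation with 4 weeks of treatment and a start delay of 0 to 1 month gives 43% to 40%. The timing assumption matters:
- even spread to 36 months: 28% to 26%
- even spread to 60 months: 17% to 15%
- all events between 6 weeks and 12 months: 68% to 64%

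**4. Events and pause probabilities per arm.** The protocol gives no late rate for this treatment. The 2% row is in line with the roughly 2% grade 3 or higher toxicity, acute and late, in two studies cited in Background; 10% and 20% are illustrative. Take d = 1.5, a constant late hazard and 2.5% acute failures, which are counted for patients who have finished treatment. The per-patient probability of counting is q = 0.025 × 22.5/24 = 0.0234 under the present rule. If late events also count, it is q + 0.975 × r, where r is the probability of a late event known before recruitment closes. The pause probability is P(X ≥ 5) with n = 46.

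| Late rate by 24 months | Late events (46 × rate) | Known while recruiting (46 × r) | Pause, present rule | Pause, late events counted |
|---|---|---|---|---|
| 0% | 0 | 0 | 0.4% | 0.4% |
| 2% | 0.9 | 0.4 | 0.4% | 1.4% |
| 10% | 4.6 | 1.9 | 0.4% | 17% |
| 20% | 9.2 | 3.9 | 0.4% | 55% |

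The present rule does not respond to late toxicity at all: its column is flat.

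**The case against.** The strongest reply is that late harm already has a route. Every toxicity above grade 2 goes to the safety board without a 6-week limit, late toxicity is assessed at each visit, and nothing forbids a pause on other grounds. Tying an informal pause to the primary endpoint of a pilot study is coherent. This stands in part. A reader might infer that late harm goes unmonitored, that the board cannot pause the trial, or that therapy stops never reach it. The article does not support any of these. It is a condensed account, and the board's remit would normally sit in the full protocol. It also does not say whether the board is independent. What remains is that the one stated criterion for a hold excludes late events.

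A reader might also infer that most late events arise while recruitment is open. The timeline does not show that. An even spread gives a minority, and a majority needs a mean onset before about 10 to 11 months after treatment. No section gives such timing, nor the timing of the individual harms listed in Background.

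The low-rate argument stands too. The studies cited in Background report 2% or no severe toxicity, and at 2% only about 0.4 late events per arm would be known in time. The threshold of more than 4 was also not calibrated for a longer window: at 10% late toxicity the amended rule would pause in only about one trial arm in six. These points limit the size of the concern but do not remove it. A safety rule is needed for the case in which the favourable assumption is wrong, and for hypofractionated protons the authors report nothing to test that assumption against.

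**Conclusion.** The concern holds in limited form. On the protocol's own use of the word, the hold counts only grade 3 or higher toxicity or therapy stops up to 6 weeks after treatment. That reading is an inference, since the hold sentence leaves the word undefined, but it is the only meaning the Statistics section supplies. About 40% of the late events in the 24-month follow-up would be known in time to act on, given uniform accrual and even timing; the share ranges from about 15% to 68% across the onset patterns shown. The primary analysis, sample size and error rates are unaffected. This should be changed because the gap concerns the type of harm on which the rationale rests, and closing it costs little.

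**What to change.** In the Statistics section, define the hold count explicitly. Recruitment is put on hold when, in one arm, more than 4 patients have had either a primary-endpoint failure or, at any later follow-up while recruitment is open, a grade 3 or higher toxicity. Each patient counts once. Keep the primary endpoint at 6 weeks.

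The cost is protocol wording. The events are already collected, and the hypotheses, the 41 evaluable patients per arm and the type I error do not change. The downside is a slightly higher chance of a temporary pause for discussion when treatment is in fact safe: from about 0.4% to 1.4% per arm if late toxicity is 2%, and no increase if there is none.

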## Discussion

With the conducted study we want to gain basis data of hypofractionated irradiation of the prostate with both, carbon ions and protons in terms of controlled clinical study. Referring to these experiences a confirmatory randomized study comparing carbon ion and proton irradiation will be planned. Hypofractionated carbon ion irradiation is considered as therapy standard since data from Japan are existing, however, not conducted with the raster scan technique. These data serve as historical controls to plan and to evaluate this pilot study regarding safety and feasibility of both planned study arms. Primary endpoint is the evidence of the safety and feasibility of the study treatment on the basis of incidence grade III and IV NCI-CTC-AE (v. 4.02) toxicity and/or the dropout of planned therapy due to any reason.

Both study treatments (arm A: protons; arm B: carbon ions) will be tested separately, but randomized, in a non-inferiority trial for the primary endpoint toxicity since the efficacy of both radiotherapeutical approaches is comparable. The non-inferiority/inferiority is quantified separately by means of the historical control. The question which arm has the advantageous toxicity is evaluated exploratively to plan consecutively a confirmatory study for a full evaluation of efficacy and feasibility of hypofractionated irradiation of the prostate with protons and carbon ions in prostate cancer patients in an active beam technique.

For each of both arms the same non-inferior level of toxicity is chosen and with a width of 10% fits the purpose of a pilot study similarly as the chosen statistical type I error probability of 10%. The calculation of the number of cases occurs on the basis of the both non-inferior questions in comparison to the standard calibrated at the toxicity rate of maximal 2.5% from the current standard (supported by the Japanese results with no reported toxicity).

Randomization will guarantee comparability of both study arms by a balanced patient population in both groups but is not intended for a confirmatory comparison of both arms. Parallel group comparisons are conducted as secondary comparisons.

Aim of the pilot study is the evaluation of the safety and feasibility of hypofractionated irradiation of the prostate with protons and carbon ions in prostate cancer patients in an active beam technique. Additionally, the results of the carbon ion irradiation of the Japanese study are compared in terms of toxicity. A toxicity analysis of the same fractionation scheme with protons will be opposed to the results of the carbon ion irradiation. PSA-PFS, OS and QoL are secondary outcome measures.

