Due to physical characteristics, ions like protons or carbon ions can administer the dose to the target volume more efficiently than photons since the dose can be lowered to the surrounding normal tissue. However, parts of the risk organs remain in the target volume: base of bladder, urethra and the facing wall of the rectum. The tolerance dose of the urethra, which is in the center of the target volume, is >85 Gy. A prospective study with a fraction scheme of 48 × 1.8 Gy = 86.4 Gy reported the appearance of urethral strictures in <3% of the patients [10]. For both, the bladder and rectum, studies found a high volume effect. The TD 5/5 for radiation of 2/3 of the bladder is 80 Gy, whereas it is 65 Gy for radiation of the whole bladder [11]. For the rectum, a high volume effect is known as well [12]. With ion radiation, it is possible to spare especially the posterior rectum wall in comparison to photon radiation, so potentially receiving also a more efficient regeneration of the anterior rectum wall. For proton irradiation, we know the data of the retrospective analysis of Loma Linda [13], as well as the randomized study of Boston, in which proton boost to a TD of 79.2 Gy vs. 70.2 Gy was used after a radiation of photons. The authors showed a significant advantage for high doses with an acceptable occurrence of adverse effects (2% acute and chronic toxicity < of CTC grade 3 or higher) [6].

Due to its mass, carbon ions have a higher biological efficacy than protons with comparable dose profile. Several trials using carbon ions in a dose escalating manner were performed by the group of researchers in Chiba/Japan. A total of 176 patients were treated with a dose of 20 × 3.3 GyE. The 5-year biochemical recurrence free survival rate was up to 83.2% for all patients and 100% for patients with low risk prostate cancer. No late toxicity of CTC grade 3 or higher was found [3]. However, the region of the anterior rectum wall was only strained to 50-90% of the dose.

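### A pass on the primary test shows 6-week safety and feasibility against a fixed 87.5% threshold; it does not show toxicity non-inferior to the Japanese carbon-ion standard

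*Protocol article*

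**What the plan says.** **Question.** Statistics poses two co-primary questions, one per arm. For carbon ions it asks: "Is the toxicity of carbon ion irradiation (arm B) non-inferior compared to standard radiation". The proton question has the same form.

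**Endpoint.** Under Evaluation of safety and Statistics, a patient is a success if no toxicity of grade 3 or higher occurs from the start of radiotherapy to 6 weeks after its end, and therapy is not stopped for any reason. Evaluation of safety defines that window as acute: "Acute events are defined to arise within 6 weeks after end of treatment".

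**Test.** Each arm is tested alone by a one-sample binomial test of a success rate of 87.5% against 97.5%, with alpha 10%, power of at least 90% and 41 evaluable patients.

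**Benchmark.** The Discussion treats hypofractionated carbon-ion irradiation as the standard and says of the Japanese data: "These data serve as historical controls to plan and to evaluate this pilot study regarding safety and feasibility of both planned study arms". It adds: "The non-inferiority/inferiority is quantified separately by means of the historical control". The margin is 10 percentage points, and the standard is calibrated at a toxicity rate of at most 2.5%, "supported by the Japanese results with no reported toxicity".

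**What is known of that control.** Background reports: "A total of 176 patients were treated with a dose of 20 × 3.3 GyE". On toxicity it says: "No late toxicity of CTC grade 3 or higher was found". Nothing else is given on toxicity in that series.

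**The concern.** The stated question is about toxicity relative to a standard, and the named source for the standard is the Japanese series. The article reports that series for late toxicity only. The primary endpoint closes where the article's late period begins, and it adds therapy stops, for which no historical figure is given. The Discussion drops both qualifiers, late and grade 3 or higher, when it cites the series in support of 2.5%.

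What is at stake is the sentence the trial may write at its end. A pass could be reported as toxicity non-inferior to carbon-ion standard treatment, and the planned confirmatory trial would build on that, with no matching rate for the standard behind it. A miss could equally be read as a toxicity problem when it arose from patients stopping for reasons unrelated to toxicity.

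**Working it through.** **1. Reproduce the plan's figure.** Inputs from Statistics: success 87.5% against 97.5% (failure 12.5% against 2.5%), alpha 10% (taken as one-sided, since sidedness is not stated), power at least 90%. With X failures among n patients, find the smallest n and cut-off c with P(X ≤ c | 0.125) ≤ 0.10 and P(X ≤ c | 0.025) ≥ 0.90. The result is n = 41, c = 2:

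- alpha = 0.00419 + 0.02455 + 0.07014 = 0.0989 (0, 1 and 2 failures at 12.5%)
- power = 0.35415 + 0.37231 + 0.19093 = 0.9174 (the same at 2.5%)

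The stated 41 per arm is correct.

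**2. What a pass shows.** With 2 failures in 41, the exact one-sided 90% upper limit for the failure rate is 12.46%. A pass therefore places the 6-week composite failure rate below 12.5%, and with it the rate of acute toxicity of grade 3 or higher. This is an absolute statement.

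**3. When a pass also means non-inferior within 10 points.** Let s be the standard's own 6-week composite failure rate. The margin claim needs the arm's rate to be below s + 10 points. The test shows that it is below 12.5%, so the claim follows only if s ≥ 12.5 − 10 = 2.5%. The effective margin is 12.5 − s.

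The documents do not give s. For assumed values, with success at 2 or fewer failures in 41:

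| s (assumed) | Effective margin | P(pass), arm 10 points worse than s | P(pass), arm equal to s |
|---|---|---|---|
| 0% | 12.5 points | 0.21 | 1.00 |
| 2% | 10.5 points | 0.116 | 0.95 |
| 2.5% | 10 points | 0.099 | 0.92 |
| 5% | 7.5 points | 0.043 | 0.66 |
| 7.5% | 5 points | 0.018 | 0.40 |

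Only at about 2.5% does the test have the properties claimed for a non-inferiority comparison with a 10-point margin.

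**4. Does the document supply s?**

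- Japanese series (Background): late toxicity of grade 3 or higher, none found. No acute rate and no stop rate.
- 770-patient hypofractionated series, 70 Gy in 28 fractions (Background): 2% acute and late toxicity of grade 3 or higher. Not the named control; stops not counted.
- Randomized proton-boost study (Background): about 2% acute and chronic, grade wording garbled. Not the named control; stops not counted.

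None is a 6-week rate of toxicity plus stops for the carbon-ion standard.

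**5. What a late-toxicity comparison could show.** Exact one-sided 90% upper limits, assuming all 41 patients in an arm are followed to 24 months: 0 events, 1 − 0.10^(1/41) = 5.46%; 1 event, 9.16%; 2 events, 12.46%. For the Japanese series at the same level, assuming all 176 are evaluable: 1 − 0.10^(1/176) = 1.30%. The comparison is feasible but imprecise, which suits a descriptive role.

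**The case against.** Several stronger readings are tempting, and the documents do not support them.

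- *The 2.5% is purely a late-toxicity figure.* Statistics rests it on favorable published results in general, the Discussion says only that the Japanese results support it, and two series in Background give rates near 2% that include acute toxicity. As a planning assumption 2.5% is not unreasonable. What those series do not supply is a 6-week rate, with stops, for the named standard.
- *The control and the endpoint share no event.* That goes beyond what can be seen. The cited Japanese publication may report acute results, and the Discussion's phrase may reflect them. The article does not show it.
- *The primary test cannot answer its question.* As a test of 6-week safety and feasibility against a fixed threshold it is valid and correctly sized. An acute primary endpoint with late toxicity as secondary is a legitimate choice for a pilot.
- *Late toxicity is overlooked.* Work-up schedules toxicity assessment to 24 months, with at least yearly contact afterwards. Evaluation of safety makes time to toxicity above grade 2 a secondary endpoint. The Abstract and the end of the Discussion plan a comparison with the Japanese results, though without naming an endpoint or time window.
- *A missed threshold would show inferiority.* Failing to reject the null shows no such thing, and the endpoint openly includes stops.

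These points remove any criticism of the test and most of any criticism of the 2.5%. The non-inferiority label remains unsupported.

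**Conclusion.** The point holds as one about what the primary result may be said to show. A pass (2 or fewer failures in 41) supports a 6-week composite failure rate below 12.5%. It does not establish toxicity non-inferior to the Japanese carbon-ion standard, because the article gives no rate for that standard on the composite endpoint. A miss may reflect stops unrelated to toxicity.

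Over assumed standard rates of 0% to 7.5%, the effective margin runs from 12.5 down to 5 points, and the chance that an equally good arm passes falls from 1.00 to 0.40. These figures assume a one-sided alpha and exactly 41 evaluable patients. The sample size needs no correction on this ground.

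**What to change.** 1. State the primary conclusion, per arm, as 6-week safety and feasibility against a fixed 87.5% threshold. Drop the non-inferiority and historical-control language from it, unless a rate of acute toxicity plus discontinuation is cited for the standard.
2. Report toxicity of grade 3 or higher and therapy stops separately beside the composite, so that a miss can be interpreted.
3. Make the planned Japanese comparison on late toxicity of grade 3 or higher, per arm, from the data already collected to 24 months, with exact confidence limits at one common level. Keep it descriptive, not a condition for calling the regimen safe, and note the differences in follow-up and beam technique.
4. Reconcile the Discussion's statement on Japanese toxicity with the narrower one in Background, going back to the cited publication to see which is accurate.

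Cost: wording and a small amount of extra tabulation, with no added patients or visits. The downside is a narrower headline claim.
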